## Abstract

**Background:**

Manual Therapy applied to patients with non specific neck pain has been investigated several times. In the Netherlands, manual therapy as applied according to the Utrecht School of Manual Therapy (MTU) has not been the subject of a randomized controlled trial. MTU differs in diagnoses and treatment from other forms of manual therapy.

**Methods/Design:**

This is a single blind randomized controlled trial in patients with sub-acute and chronic non specific neck pain. Patients with neck complaints existing for two weeks (minimum) till one year (maximum) will participate in the trial. 180 participants will be recruited in thirteen primary health care centres in the Netherlands.

The experimental group will be treated with MTU during a six week period. The control group will be treated with physical therapy (standard care, mainly active exercise therapy), also for a period of six weeks.

Primary outcomes are Global Perceived Effect (GPE) and functional status (Neck Disability Index (NDI-DV)). Secondary outcomes are neck pain (Numeric Rating Scale (NRS)), Eurocol, costs and quality of life (SF36).

**Discussion:**

This paper presents details on the rationale of MTU, design, methods and operational aspects of the trial.

**Trial registration:**

ClinicalTrials.gov Identifier: NCT00713843

## Background

Neck pain is one of the most common complaints of the musculoskeletal system.

Approximately two thirds of the population will at some point in their life experience neck pain [1]. Prevalence rises with age in both sexes and is highest at ages between 50 and 59. In general women suffer from neck complaints twice as often as men.

Prevalence of neck complaints is between 10% and 15% [2]. In the Netherlands, the point prevalence in absolute figures, calculated in the year 2000, amounted to 594,000 males and 1,013,700 females registered with chronic neck complaints [3]. Systematic reviews showed a considerable heterogeneity in prevalence of neck complains. Fejer et al found a range of the one-month prevalence from 15.4% to 41% [4]. Hogg-Johnson found a range from 15.4% to 45.3% among adults, interfering with activities ranged from 7.5% to 41.5% [5]. Bot showed an incidence of 23.1 per 1000 person-years of neck symptoms in a Dutch national survey of general practice [6].

The total costs related to neck pain in the Netherlands added up to approximately 668 million Euros in 1996. Direct medical costs amounted to 160 million Euros (23% of the total costs related to neck complaints) [2]. Allied health care (such as occupational therapy and physical therapy) made up the largest proportion of the direct costs (84%) [2]. As such, neck pain forms a significant personal and economical problem.

Neck pain can be caused by traumata (specifically traffic accidents), infections, tumours, congenital defects and inflammations; however in many cases it is not possible to determine the underlying cause. In these cases neck pain will be regarded as 'non-specific neck pain'.

In case of acute neck pain the general practitioner (GP) will usually not take immediate action. Pain medication might be prescribed [7]. Research by Vos indicates that 51% of patients having neck pain are referred to physical therapy or manual therapy [7].

These figures may differ internationally because of different referral policy.

If the complaints are persistent (for six months or longer) it appears that the average discomfort perceived will remain fairly stable [8]. It is clinically and economically relevant to ensure that patients do not end up in this chronic phase.

### Level of evidence manual therapy

In 2004 Gross et al made a meta-analysis of Randomized Controlled Trials (RCTs) in which the effect of manipulations and mobilizations for mechanical neck complaints was investigated [9]. In cases of a single manipulation session or several sessions (3 to 11 weeks) of manipulations or mobilizations compared to a control group or when mobilizations were compared to other forms of therapy, moderate evidence was found that this gave no results in the short term for acute, sub-acute and chronic mechanical neck problems.

When manipulation and mobilization were compared to withholding treatment, the results showed a tendency towards a positive effect of manipulation and mobilization. Mobilisation and manipulation compared to placebo or control groups showed a nonsignificant result [9].

Their conclusions where that the evidence did not favour manipulation and/or mobilisation done alone or in combination with various other physical medicine agents; when compared to one other, neither was superior.

As for the costs of care, there was moderate evidence that manual therapy was less expensive than other forms of care in acute, sub-acute and chronic neck complaints with or without headache or cervical radicular signs [9].

In 2007, Vernon et al published a systematic review of applying manual therapy in cases of neck pain [10]. Little evidence was found about the application of manual therapy for acute neck pain (existing less than four weeks) [10]. There was moderate- to high-quality evidence that subjects with chronic neck pain show clinically important improvements from a course of spinal manipulation or mobilization, using intragroup changes [11]. The Task Force on Neck Pain stated that manual therapy or exercise therapy was not clearly superior to one other in either short- or long-term [12].

In some countries manual therapy has been included in the guidelines for treatment of neck pain [11].

In summary, reviews showed that manual therapy is an effective method (intragroup changes)(specially in sub acute and chronic neck pain) but compared to controls there is in general no clear evidence that one of them is superior (intergroup changes).

### Research in the Netherlands

In the Netherlands, the effectiveness and cost-effectiveness of treatments with manual therapy and physical therapy (PT) compared with counselling of the general practitioner (GP) for non-specific neck pain was investigated in a RCT [13].

MT consisted of mobilizing techniques as described by Van der El en Di Fabio [14,15]. Low-amplitude, high-velocity thrust techniques were not applied. After seven weeks, perceived recovery was 68% for MT, 51% for PT and 36% for GP treatment. MT scored statistically significantly better than the other interventions. PT scored better than GP, although this difference was non-significant. At one year follow-up there were no statistically significant differences between the groups for pain and impediment (global perceived effect after one year 72% MT, 63% PT and 56% GP) [16]. MT was significantly more cost-effective than treatment by the GP and physical therapy [17]. The total costs per patient, including absence from work and costs of health care utilisation, amounted to €447 for MT, €1297 for PT and €1379 for GP.

In later research by Pool et al manual therapy (MT) was compared with exercise therapy with behaviour graded activity (BGA) in people with neck complaints [18]. Pool found neither clinically relevant nor statistically significant differences. 89.4% in the BGA group and 86.5% in the MT group showed positive global perceived effect after 52 weeks.

So, although the systematic reviews did not clearly show an effect of manual therapy for neck pain, two Dutch studies found that manual therapy is more cost-effective than physiotherapy and GP counselling, and equally effective as an extensive exercise therapy with behaviour graded activity programme. However, in both Hoving's and Pool's studies other forms of manual therapy than MTU were used [13,19].

### Manual therapy according to the Utrecht School (MTU)

MTU is based on assessing the patient's individual preference of functioning by documenting and interpreting their natural asymmetry in anatomical form, posture and movements.

The normal asymmetry and variability of human form and movement function have been specified in research [20-26]. These studies showed that many movements are carried out asymmetrically. These asymmetrical forms can be related to the asymmetrical movement function.

In addition to the general diagnostics, MTU is characterized by specific diagnostics. By means of this specific manual-therapeutic analysis the individual preference of functioning model of the patient is drawn up through documentation and interpretation of the individual asymmetry in form, posture and movement [27,28]. Some explanations of the measurements and movements are: (preferred) hand folding; (preferred) arm folding; which eye is master eye; leg use in (preferred) kicking of a ball. The purpose here is to describe the optimal direction and position of movement axes for all joints according to this model.

When composing this model, firstly the individual characteristics (a number of preferred movements, a number of asymmetrical aspects of posture and form) are assessed. Documentation, notation and interpretation of these characteristics take place according to a protocol.

The objective of MTU is to optimise the positioning of movement axes in the joints. To achieve this, three-dimensional movements in the joints are executed repeatedly. To purpose fully position the movement axes the therapist should (repeatedly) perform passive joint movements with low velocity and high accuracy. In addition to examining the individual preference of movement, exploratory examination is carried out to recognise possible red flags and to determine the treatment indication.

Treatment is based on preferred movements found in the patient and the interpretation according to the protocol of these movements and not on the complaint of the patient. It is executed by applying passive articular movements in the spinal joints and the joints of the extremities. During this process physiological joint limitations are carefully observed; traction or high-velocity movements will not be applied, as may be the case in other forms of manual therapy [29].

The diagnostic examination of other forms of manual therapy focuses on joint function, stability, movement patterns, range of movement, and the severity of disorders [30]. To diagnose the patients complaints, palpation of passive accessory and passive intervertebral movements are used. The results yield information as to tenderness (pain), restricted intersegmental motion (stiffness), and spasm (muscle tension) [29-31].

In general, other manual therapies, as described by Veen et al, are directed primarily to the complaints of patients, particularly the main complaint [29,32].

### Trial Objectives

The primary objective is to compare the short-term effectiveness (7 weeks) and long-term effectiveness (52 weeks) of MTU with physical therapy in patients with sub-acute and chronic neck pain with regard to global perceived effect, functioning and pain.

The cost-effectiveness of manual therapy compared with physiotherapy will also be evaluated.

## Methods/Design

### Design and setting

This research is a single-blinded randomized controlled trial with cost-evaluation. A central research centre is set up in the Radboud University Nijmegen Medical Center, the Netherlands, housing a central investigator, an advisor, an independent physician, a statistician and a blinded research assistant entering data.

There are twelve locations where patients are treated. All of these are primary health care centres for manual and/or physical therapy. Each local centre will have a manual therapist, a physical therapist and a research assistant.

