### Sample size

The sample size is based on one of the two primary outcome variables, Neck Disability Index (NDI) and Global Perceived Effect (GPE). The GPE is chosen, because this outcome variable needs the largest group of participants. Previous studies have shown that the effect of manual therapy on GPE is 68.3% [13] and 70.1% [18].

A 20% difference on the GPE scale is considered clinically relevant. Based on α = .05 and an 80% power (β = 0.2) 76 participants per intervention group are required.

With regard to prospective drop outs (15%), 90 participants per group will be recruited in this trial. A similar sample size was used in previous research [19,34,35].

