#### Randomisation, blinding and allocation

Block randomisation will take place through the computer after pre-stratification on the basis of prognostic aspects for the complaints: level score of the main complaint (scale 10: <7 or ≥ 7) and age (< 40 or ≥ 40 years) [59,60].

Four groups are formed which are randomized for both intervention groups. The randomisation scheme will be generated by the central computer. The LRA is blinded for the randomisation.

Treatment with physical therapy and MTU will take place at different locations. The investigator in charge of the database has no access to the key of the combination patient data - research number - treatment allocation. In the case of missing data the computer system will automatically generate an email to the participant directly or to the secretary of the NECKprojectgroup. The computer or secretary will send the patient a standard reminder. None of the therapists know the patient number(s).

The data from the questionnaires filled in digitally on http://www.neckproject.nl are sent directly to the database of the central researcher. The researcher is blinded from patients' data and type of intervention. The questionnaires filled in by hand are sent to a central freepost address. These lists are entered into the database by a secretary. Loss of data should be prevented by actively reminding the patient by email, mail or telephone.

Patients who fill in the forms digitally will automatically receive a reminder by email. Patients who fill in the lists by hand will receive them through the post. The secretary will attend to this.

Each treatment sessions will be registered by using standard forms filled in by the therapist. By doing spot checks the information received about the content of the treatment session will be inspected by the researcher from the UMC St Radboud.

Visitations will take place to ensure the therapists in attendance are keeping to the research protocols.

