#### Multi-variate analysis

An ANOVA will be used to analyze differences between conditions per person (within subject) and per group (between groups).

Descriptive statistics will be applied to make a comparison between the baseline data of the manual therapy and the physical therapy groups and to assess whether the randomisation has been successful. Group differences between the interventions with a 95% confidence interval will be calculated for all outcome measures.

The statistical analyses will be carried out according to the intention-to-treat principle, whereby the patients are analysed in the intervention group in which they were originally placed. The differences between groups will be tested by ANOVA/mixed model (continuously) and by the Chi-Square test for dichotomous variables.

Multi-variate regression analysis will be used to test the influence of the baseline variables on the outcomes.

For the primary outcome measure Global Perceived Effect (GPE) a selection can be made between responders (positive effect) and non-responders (no or negative effect) to the treatment received.

The data will be processed by SPSS/SAS statistical software.

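### The sample size and the chi-square test for GPE treat patients as independent, although each arm is delivered by only about 12 to 13 therapists

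*Protocol article*

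**What the plan says.** *Design and setting* gives the delivery structure: "There are twelve locations where patients are treated", and "Each local centre will have a manual therapist, a physical therapist and a research assistant". The abstract counts thirteen centres. Under *Physical therapy (comparison intervention)*, physical therapists who have trained, or begun training, as manual therapists are not selected, so no therapist works in both arms. *Randomisation, blinding and allocation* adds that "Treatment with physical therapy and MTU will take place at different locations" and stratifies on main-complaint score and age, not on centre or therapist.

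*Sample size* is driven by GPE, with 20 points as the target gap between arms: "Based on α = .05 and an 80% power (β = 0.2) 76 participants per intervention group are required". An allowance of 15% for dropout takes recruitment to 90 per group. No ICC, design effect or therapist term appears.

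*Multi-variate analysis* fixes the tests: "The differences between groups will be tested by ANOVA/mixed model (continuously) and by the Chi-Square test for dichotomous variables". The same section says that GPE can be split into responders and non-responders, which matches the percentages used in the sample size.

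**The concern.** Patients who share a therapist tend to have similar outcomes, particularly when both treatments are hands-on and tailored to the patient. Because each therapist belongs to one arm only, differences between therapists do not cancel in the MTU versus physical therapy comparison. They add to its variance. A chi-square test on responder counts ignores that component.

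If the component is not negligible, the test rejects too often, and a few unusually good or poor therapists can pass for a treatment effect. A test that does account for it has less power at 76 per group than the protocol states. GPE is both a primary outcome and the basis of the sample size, so the problem falls on the main comparison.

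**Working it through.** **Inputs from the protocol article.** Alpha 0.05, 80% power, 76 analysed and 90 recruited per group, 15% dropout, a 20-point GPE difference, and manual therapy rates of 68.3% and 70.1% (*Sample size*); one manual and one physical therapist per centre and twelve locations (*Design and setting*); thirteen centres (abstract). **Assumed:** ICCs of 0.01 to 0.10, equal therapist loads, and a two-sided test, since sidedness is not stated.

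**The plan's own figure.** For two independent proportions, n per group = [z_a·√(2·p̄·q̄) + z_b·√(p1·q1 + p2·q2)]² / d², with d = 0.20.

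- One-sided, 68.3% vs 48.3%: (1.645 × 0.697 + 0.842 × 0.683)² / 0.04 = 74.1, so 75. For 70.1% vs 50.1% the result is 74.
- Two-sided with continuity correction, 68.3% vs 88.3%: 66 before the correction and 76 after it.
- Two-sided with the comparator 20 points lower: 95 and 93, which does not reproduce 76.

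The comparator rate is not stated either, so the route actually used cannot be identified. Every route that gives or comes close to 76 is a formula for independent patients. Dropout: 76 / 0.85 = 89.4, so 90. The whole step from 76 to 90 is spent on dropout, and nothing is left for clustering.

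**Adding clustering by therapist.** With 12 therapists per arm, m = 76 / 12 = 6.33 analysed patients each.

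- Design effect: DE = 1 + (m − 1) × ICC = 1 + 5.33 × ICC
- Type I error of the unadjusted test: 2 × [1 − Φ(1.96 / √DE)]
- Power of a correctly adjusted test, from the stated 80%: Φ[(1.96 + 0.842) / √DE − 1.96]
- Analysed n per group to keep 80%: 76 × DE, rounded up; recruited n is that divided by 0.85

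| Assumed ICC | DE | Type I error, unadjusted | Power, adjusted | n analysed (recruited) per group for 80% |
|---|---|---|---|---|
| 0.01 | 1.05 | 5.6% | 78% | 81 (96) |
| 0.02 | 1.11 | 6.2% | 76% | 85 (100) |
| 0.05 | 1.27 | 8.2% | 70% | 97 (115) |
| 0.10 | 1.53 | 11.4% | 62% | 117 (138) |

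Example at ICC 0.05: DE = 1 + 5.33 × 0.05 = 1.27; 2.802 / √1.267 = 2.489; 2.489 − 1.96 = 0.529; Φ(0.529) = 0.70.

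**Sensitivity to the structure.** With 13 therapists per arm, adjusted power is 78%, 76%, 71% and 63%. If different locations means that the twelve locations are split six per arm (an assumption), m = 76 / 6 = 12.7. Adjusted power is then 76%, 71%, 61% and 48%, and the unadjusted type I error is 6.4%, 7.8%, 11.9% and 18.3%.

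**The case against.** Five points can be made for the plan.

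1. **NDI and NRS.** A reader might infer that their analysis also assumes independence, because ANOVA is named. The sentence allows a mixed model for continuous outcomes, and which random effects it carries is properly left to an analysis plan that is not shown. This stands: no error is established for those outcomes.

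2. **Size of the power loss.** A reader might start from about 71% power (a two-sided test of 68.3% vs 48.3% with 76 per group) and conclude that therapist effects bring the planned test down to about 52% at ICC 0.10. The document does not support this. The 71% comes from unstated sidedness and comparator rate, which is a separate sample-size matter. The fall is also that of an adjusted analysis. For the chi-square as planned, power is Φ(0.842 / √DE) from the stated 80%, that is 79%, 77% and 75% at ICC 0.02, 0.05 and 0.10. It loses little power because it does not hold its type I error.

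3. **Unknown ICC.** The consequence depends on a value that the document does not give. Some features should limit therapist variation: at least five years of experience in both arms, protocol-based measurement and interpretation in MTU, session forms, spot checks and visitations. This stands as a reason to state the consequence conditionally. It does not show that the ICC is zero.

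4. **Shared centres.** If each centre serves both arms, the common centre effect largely cancels, and ignoring it is conservative for that component. This also stands. The ICC in the table must therefore be read as therapist-level correlation only.

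5. **Cluster count.** Twelve therapists per arm is a reading of the text, and the statement on different locations fits poorly with both therapists being in each centre. This is correct, and it is why a range is shown. A split of locations by arm would make the loss larger.

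**Conclusion.** The point holds for GPE and for the sample size. The 76 per group has no allowance for therapist clustering, and the test fixed for dichotomised GPE cannot make one. If outcomes correlate within therapist, the GPE standard error is understated, and a valid analysis with 76 per group falls short of 80% power.

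The size is conditional. Over assumed therapist-level ICCs of 0.01 to 0.10 with 12 therapists per arm, type I error runs from about 5.6% to 11.4% and adjusted power from about 78% to 62%. At 0.01 the effect is minor; from about 0.05 it matters. These figures assume equal loads and large-sample approximations, and start from the stated 80%. They do not show that therapist effects exist in this trial, and they do not extend to NDI or NRS. The issue should be corrected, but it does not undermine the design.

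**What to change.** - **GPE:** replace the chi-square test with a logistic mixed model or GEE clustered on treating therapist, with a small-sample correction suited to about 24 to 26 clusters.
- **NDI and NRS:** drop the plain ANOVA option and use the mixed model already allowed, with a random intercept for therapist.
- **Power:** restate it for 76 analysed per group over an assumed ICC range, giving the cluster size used.
- **Structure:** reconcile the abstract, *Design and setting* and *Randomisation, blinding and allocation* on the number of centres and where each arm is treated.

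The cost is small: slightly wider intervals, a less favourable stated power and a somewhat more complex model. No extra patients or data are needed, because the envelope handed over at randomisation already names the therapist. A coded therapist identifier linked to the analysis data would be enough.

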### Ethical approval

Ethical approval was obtained from the Medical Ethics committee CMO Arnhem-Nijmegen (NL21128.091.08).

### Inclusion and exclusion

Males and females aged between 18 and 70 years having neck pain for at least two weeks and with the last episode started at maximum of 52 weeks ago are eligible. Neck pain is the primary pain at the time of inclusion and must be provoked and reproduced as mechanical neck pain by movement or posture of the neck. Participants may have cervicogenic headache and radiation to the elbow. Exclusion criteria are: presence of red flags such as specific neck pain caused by cervical radiculopathy, entrapment neuropathy, myelopathy, unexplained fever, unexplained weight loss, nocturnal persistent pain, general malaise [33]; surgery of the cervical spine; pregnancy; whiplash trauma (in the past or recent, as cause of the complaint); physical conditions seriously impeding treatment (such as amputations, being wheelchair bound, illness); insufficient knowledge and command of the Dutch language for answering the questionnaires (to be judged by the research assistant); therapeutic treatment for neck pain in the previous three months such as physical therapy, manual therapy, osteopathy, chiropractics and acupuncture.

